### Exclusion criteria

Epilepsy.Neurological disorders.Current episode of neuropsychiatric disorders such as schizophrenia spectrum disorders, major depressive disorders or bipolar affective disorders.Suicidality (acute).Use of antiepileptic or high-potent neuroleptic drugs.Current substance use disorder other than alcohol, nicotine and severe cannabis use disorder according to DSM-5.Implants (e.g., vagus nerve stimulator, cerebral shunt).

### Clinical measures

Several clinical as well as psychological measures will be included in the pre and post treatment assessments. Clinical interviews such as the SCID-5 as well as questionnaires will be used to evaluate patients’ drinking behaviour (retrospective quantity–frequency questionnaire as part of the M-CIDI (Munich Composite International Diagnostic Interview [47]), dependence severity (ADS [48]) as well as craving (AUQ [49], OCDS [50]). In addition, we will assess measures such as affective and anxiety symptoms (ADS [51], PANAS [52], STAI [53]), impulsivity (BIS-15 [54]), stress (TICS [55], PSS-10 [56]), trait and state mindfulness (FFA [57], FFMQ [58]). Furthermore, we will include various measures that could impact treatment outcome, such as abstinence self-efficacy (AASE [59]), psychological flexibility (PsyFlex [60]) and willingness to change (URICA [61]). All questionnaires will be completed before and after the intervention. To assess long-term treatment effects, patients will be followed-up after three months to assess abstinence days and alcohol consumption (heavy drinking days, total drinking days).

### MBRP

Detoxified AUD patients will be enrolled in a rolling format MBRP group therapy that consists of six weekly sessions and daily stand-alone practice of mindfulness techniques (independently performed by the participants between sessions). All participants will receive a psychological one-on-one consultation before start of MBRP to boost motivation to participate as well as convey general information about the structure of the program. MBRP group therapy will be administered by trained staff members and according to manuals by Bowen et al. [62] and Roos et al. [63] that were modified to accommodate six sessions in a rolling format. Further, group leaders receive regular/biweekly/monthly supervision by an experienced group psychologist/supervisor to ensure quality of MBRP group therapy during the study.

### Psychophysiological data

#### Tasks

Before and after treatment we will assess cognitive control with a hybrid of the Simon and go/no-go paradigms (Simon go/no-go; SGNG) that has been shown to engage frontal midline regions [46, 64]. Furthermore, we will assess physiological cue reactivity with a passive viewing task that adheres to the guidelines provided by Ekhitiari et al. [65], along with measures of subjective cue-induced craving. Finally, to evaluate the effect of tVNS on interoceptive accuracy, participants will complete a heartbeat discrimination task (HDT) that is based on the one that was developed by Critchley et al. [66].

#### EEG and HRV

32-channel EEG will be recorded using active Ag/AgCl electrodes (actiCap GmbH, Wörthsee, Germany). Recordings will be collected using a LiveAmp amplifier (Brain Products GmbH, Gilching, Germany). Data will be acquired at a sampling rate of 500 Hz and impedances will be kept below 10 kOhm. MNE-Python [67] will be used to analyze EEG data. The signal will be bandpass-filtered between 1 and 40 Hz, and the PREP pipeline [68] will be used to reject/repair bad sensors and segments. Morlet wavelets (1 to 40 Hz in 0.5 Hz steps, 7 cycles per wavelet) will be used to obtain a time-frequency transform of the data [69]. Finally, differences between conditions will be assessed using a cluster-based permutation test across all sensors and frequencies [70]. In this manner, we will assess whether changes in the EEG are specific to the theta frequency band.

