#### CLAM- tACS

In analogy to the tVNS condition, CLAM-tACS will be conducted during a mindfulness exercise. We will employ a Digitimer DS5 (Digitimer Ltd, Hertfordshire, UK) to deliver amplitude-modulated transcranial alternating current stimulation (AM-tACS) through two circular rubber electrodes (4 cm ⌀) centered on positions Fpz and Cz of the international 10–20 system. Personalized current flow modeling will be used to optimize the tACS electrode montage and maximize target engagement (Kasten et al., 2019). The AM-tACS stimulation waveform will feature a carrier signal frequency of 8 kHz, an amplitude of ± 1 mA, and an envelope signal that is phase-tuned to frontal midline theta oscillations in real-time. Previous studies have shown that tACS at frequencies in the kHz range is a safe and effective approach to modulate cortical excitability [72]. EEG will be recorded using a 64-channel Bittium NeurOne system (Bittium, Oulu, Finland), which will deliver a real-time UDP stream to a Speedgoat Performance Real-Time target machine (Speedgoat GmbH, Liebefeld, Switzerland) that will apply artifact suppression and real-time phase estimation of frontal midline theta oscillations. The target machine will deliver the stimulation signal to the Digitimer DS5 in real-time. To assess phase-dependent effects of CLAM-tACS on FMΘ, we will bandpass-filter the data from 4 to 8 Hz using an FIR filter. Subsequently, SASS will be applied to suppress the stimulation artifact [43]. Finally, the Hilbert transform will be used to obtain instantaneous amplitude and phase of FMΘ. Instantaneous phase will be used to verify correct phase-locking between CLAM-tACS and FMΘ, and instantaneous amplitude will be used to assess enhancement or suppression of FMΘ.

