### Sample size

For the examination of the effect of tVNS, we based our sample calculations on a study that investigated the effect of tVNS on protracted alcohol withdrawal symptoms in abstinent AUD patients [73]. According to the changes in the craving scores, considering a 95% confidence interval, 80% power (α = 0.05), and the related mean and standard deviation (SD) of the craving scores in the aforementioned study (μ1 = 4.82; μ2 = 3.92; SD1 = 0.49; SD2 = 0.39) we estimate *n* = 40 for each group. With an attrition rate of 20%, final estimated sample size is *n* = 50 per group. With regards to the application of CLAM-tACS, we performed a sample size estimation on the basis of a similar study investigating the causal role of frontal theta oscillations in a clinical population [74]. There, a medium effect size of dz = 0.577 was found, which corresponds to a sample size of *n* = 20 per group at a power of 0.8 und an alpha level of 0.05. In total we will recruit *n* = 140 AUD patients to be included in this study.

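### The all-sensor, all-frequency cluster test is a valid omnibus test, but it cannot establish that an EEG change is specific to theta

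*Protocol article*

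**What the plan says.** The EEG and HRV section fixes the recording, the transform, the test and the inference for the EEG recorded with the assessments before and after treatment:

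- Recording: "32-channel EEG will be recorded using active Ag/AgCl electrodes".
- Transform: "Morlet wavelets (1 to 40 Hz in 0.5 Hz steps, 7 cycles per wavelet").
- Test: "differences between conditions will be assessed using a cluster-based permutation test across all sensors and frequencies".
- Inference: "In this manner, we will assess whether changes in the EEG are specific to the theta frequency band".

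The section names no contrast of theta with another band and no frontal-midline sensor set.

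The CLAM-tACS section has a separate analysis that is aimed at theta. For phase-dependent effects of that stimulation, "we will bandpass-filter the data from 4 to 8 Hz using an FIR filter", and "instantaneous amplitude will be used to assess enhancement or suppression of FMΘ". It uses a separate 64-channel system. It does not cover tVNS or the EEG before and after treatment, and after the filter no other band is left for comparison.

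**The concern.** Specificity is a statement about a difference between effects: theta changes with treatment more than other bands do. The named procedure never estimates that difference. A reader would have to infer it from where a significant cluster begins and ends, or from the absence of clusters elsewhere, and the test supports neither inference.

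This matters because the mechanistic aim rests on theta. The abstract promises to clarify a causal link between frontal midline theta and the efficacy of the mindfulness programme, and the Background argues for engaging theta without unspecific mechanisms. The EEG and HRV section is the only place where the article says how frequency specificity will be checked. The trial could report specificity that it has not tested, or doubt it because a real theta effect spilled across the band border.

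**Working it through.** **1. Inputs.** From EEG and HRV: 32 channels, 1 to 40 Hz in 0.5 Hz steps, 7 cycles per wavelet. From CLAM-tACS: theta as 4-8 Hz. From Sample size: "a medium effect size of dz = 0.577 was found". The article gives no cluster-forming threshold, cluster statistic, noise structure or EEG effect size for the pre/post recordings, so these are assumptions below.

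**2. The plan's own figure.** No stated number lies behind the specificity sentence. The only figure tied to frontal theta is the CLAM-tACS sample size of 20 per group (dz = 0.577, power 0.8, alpha 0.05). A paired noncentral t calculation gives n = 20 with one-sided alpha (power 0.800) and n = 26 with two-sided alpha. It is used here only as the source of an effect size, taken as a between-group effect by assumption.

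**3. Search space.** (40 − 1)/0.5 + 1 = 79 frequencies; 79 × 32 = 2,528 sensor-frequency points.

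**4. What the p-value covers.** The null hypothesis is no difference between conditions at any of the 2,528 points. Rejecting it says that a difference exists somewhere. The error rate does not attach to which points belong to the cluster, so it does not attach to the cluster's lower and upper frequency. A non-significant region is one where the null was not rejected; that does not bound the effect there.

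**5. Spread from the wavelets.** With the usual Morlet convention the spectral SD is f/7, and FWHM = 2.355 × f/7 on the amplitude scale.

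- 4 Hz: 2.355 × 4/7 = 1.35 Hz
- 6 Hz: 2.355 × 6/7 = 2.02 Hz
- 8 Hz: 2.355 × 8/7 = 2.69 Hz

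On the power scale, divide by √2: 0.95 Hz at 4 Hz and 1.90 Hz at 8 Hz. The relative amplitude response of the wavelet at f to a component at 8 Hz is exp(−½[(f − 8)/(f/7)]²). At 9 Hz this is exp(−½ × 0.778²) = 0.74; at 10 Hz it is exp(−½ × 1.4²) = 0.38. A component at the top of theta is thus clearly visible above theta.

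**6. Simulation (illustrative).** Two groups on the 32 × 79 grid; cluster mass; cluster-forming threshold p = 0.05 two-sided; 150 permutations; 150-200 runs per scenario. A simulated proportion therefore has a standard error of at most √(0.25/150) = 0.041. The four settings combined noise smoothness (f/7 or constant) with effect topography (narrow or broad).

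Under the global null, false alarm rates were 0.045-0.067, so the test behaves properly as an omnibus test.

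Cluster extent at n = 40 per group (proportion of runs; results available for three settings):

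| Setting | Theta-only truth (d = 0.8): theta cluster significant | ...and runs outside 4-8 Hz | Theta (d = 0.8) plus 13-30 Hz (d = 0.3): theta cluster significant | ...and result looks theta-only* |
|---|---|---|---|---|
| f/7, broad | 0.42 | 0.40 | 0.30 | 0.11 |
| constant, narrow | 0.36 | 0.33 | 0.28 | 0.14 |
| constant, broad | 0.93 | 0.86 | 0.92 | 0.31 |

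*Nothing significant below 3 Hz or above 10 Hz.

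When the truth was theta-only, most significant theta clusters ran outside the band. When the truth was not theta-only, the result still looked so in 0.11/0.30 = 37%, 0.14/0.28 = 50% and 0.31/0.92 = 34% of the runs with a theta finding. Extent misleads in both directions.

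**7. Power, as a secondary matter.** For d = 0.577, one test on mean 4-8 Hz power at frontal-midline sensors had power 0.43-0.68 at n = 20 per group, against 0.00-0.32 for a significant cluster touching theta. At n = 40 the ranges were 0.79-0.97 and 0.00-0.63. The targeted test led in every setting, but the size of the lead varied widely.

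**The case against.** The sentence can be read modestly: the authors search the whole spectrum so that changes outside theta have a chance to appear. That reading stands in part. The search is valid, and a significant cluster away from theta would be evidence against specificity. The EEG test is also not among the declared primary analyses, which concern neurobehavioral measures, and an article may leave regions of interest, thresholds and band contrasts to a fuller plan. But the point does not rest on missing detail. The article names a procedure and the inference to be drawn from it, and the procedure can only count against specificity, never establish it.

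A reader might go further and infer that the cluster test is too weak to detect a theta effect. The documents do not support that. Power depends on choices they do not state. In a frequency-axis check (theta-only effect of 0.6 SD, 40 per group), power for a cluster touching theta was 0.11, 0.44 and 0.59 at cluster-forming thresholds of 0.05, 0.01 and 0.001. In the sensor-by-frequency simulation it reached 0.93 with a strong, broad effect (d = 0.8, n = 40, constant smoothing). A broad search that gives up power relative to a well-chosen region is partly a legitimate trade-off. For CLAM-tACS sessions, the planned 4-8 Hz amplitude analysis already tests theta directly, though without a band contrast.

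**Conclusion.** The point holds for the inference, not for the test. The cluster test is a sound omnibus test of any difference between conditions; the statement that it assesses theta specificity does not follow, and nothing else in the article supplies the missing contrast. This rests on what a cluster p-value means and on the stated wavelets, so it needs no simulation.

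The simulated 34-50% shows that a theta-only picture can arise when theta is not the only band affected. It is an illustration under assumed noise, topography, effect sizes and threshold, not a forecast for this trial. A targeted theta test would usually have more power, but the documents do not allow the gain to be quantified. The primary behavioural analyses are unaffected. The change should be made before the EEG data are analysed by arm, because bands and sensors chosen afterwards would not carry the same weight.

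**What to change.** - For the 32-channel pre/post EEG, pre-specify a frontal-midline sensor set, theta as 4-8 Hz, and the borders of the comparison bands.
- Fit one mixed model with band x arm x time (active versus sham, within each stimulation type). Base the specificity claim on pre-specified contrasts of theta with each other band. A general interaction shows only that bands differ somewhere.
- State the scale, for example log power, since a difference between bands depends on it. Consider leaving a gap next to 4-8 Hz when setting the comparison bands, because of wavelet spread.
- Report the theta arm x time effect from the same model, with confidence intervals for every band, so that small effects elsewhere are not read as none.
- Keep the all-sensor, all-frequency cluster test as an exploratory omnibus analysis, and delete the statement that it assesses theta specificity.

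No new data, visits or participants are needed. The cost is one extra model and some wording. The small downside is commitment to sensors and bands in advance, so an effect elsewhere on the scalp would appear only in the exploratory analysis.

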### Neurostimulation sessions

#### tVNS

Once a week, each group will additionally receive a 30-minute tVNS/sham stimulation during an audio-guided body scan exercise. We will employ a tVNS-R device (tVNS International GmbH, Erlangen, Germany) to deliver transcutaneous electric stimulation to the inner side of the cymba concha for optimal targeting the auricular branch of the vagus nerve. For sham stimulation, the electrode will be placed on the ear lobe which contains no branches of the vagus nerve [71]. The stimulation frequency is set to 25 Hz, which is delivered in 30 s on/off phases. In increments of 100 μA the intensity will be increased individually until subjects report mild tingling.

#### CLAM- tACS

In analogy to the tVNS condition, CLAM-tACS will be conducted during a mindfulness exercise. We will employ a Digitimer DS5 (Digitimer Ltd, Hertfordshire, UK) to deliver amplitude-modulated transcranial alternating current stimulation (AM-tACS) through two circular rubber electrodes (4 cm ⌀) centered on positions Fpz and Cz of the international 10–20 system. Personalized current flow modeling will be used to optimize the tACS electrode montage and maximize target engagement (Kasten et al., 2019). The AM-tACS stimulation waveform will feature a carrier signal frequency of 8 kHz, an amplitude of ± 1 mA, and an envelope signal that is phase-tuned to frontal midline theta oscillations in real-time. Previous studies have shown that tACS at frequencies in the kHz range is a safe and effective approach to modulate cortical excitability [72]. EEG will be recorded using a 64-channel Bittium NeurOne system (Bittium, Oulu, Finland), which will deliver a real-time UDP stream to a Speedgoat Performance Real-Time target machine (Speedgoat GmbH, Liebefeld, Switzerland) that will apply artifact suppression and real-time phase estimation of frontal midline theta oscillations. The target machine will deliver the stimulation signal to the Digitimer DS5 in real-time. To assess phase-dependent effects of CLAM-tACS on FMΘ, we will bandpass-filter the data from 4 to 8 Hz using an FIR filter. Subsequently, SASS will be applied to suppress the stimulation artifact [43]. Finally, the Hilbert transform will be used to obtain instantaneous amplitude and phase of FMΘ. Instantaneous phase will be used to verify correct phase-locking between CLAM-tACS and FMΘ, and instantaneous amplitude will be used to assess enhancement or suppression of FMΘ.

### Data management and monitoring

The conduct of the investigation and processing of all personal data will be carried out in accordance with the latest version of the General Data Protection Regulation (GDPR). The pseudonymized research data essential for the study will be stored on servers at Center for Information Services and High Performance Computing (ZIH), Dresden. To collect data, we will employ REDCap, a certified data capture system that is compliant with Good Clinical Practice (GCP) standards and FDA 21 CFR Part 11. Access to the REDCap platform is protected by an authentication process. Only authorized study personnel with a personal identifier have access to the study server. Regarding hardware used for data collection purposes (PCs, laptops), only centrally supported systems are utilized. For study consent with identifying handwritten data, pseudonymized test sheets are archived separately in an access-secured database. The data storage duration is set for 10 years to facilitate the use of data for researching the long-term development of substance use and psychiatric disorders, which necessitates such a prolonged data storage period for follow-up surveys. All participants have the right to review the collected data as well as request the blocking or deletion of their data until the reidentification list is deleted.

### Sample size

For the examination of the effect of tVNS, we based our sample calculations on a study that investigated the effect of tVNS on protracted alcohol withdrawal symptoms in abstinent AUD patients [73]. According to the changes in the craving scores, considering a 95% confidence interval, 80% power (α = 0.05), and the related mean and standard deviation (SD) of the craving scores in the aforementioned study (μ1 = 4.82; μ2 = 3.92; SD1 = 0.49; SD2 = 0.39) we estimate *n* = 40 for each group. With an attrition rate of 20%, final estimated sample size is *n* = 50 per group. With regards to the application of CLAM-tACS, we performed a sample size estimation on the basis of a similar study investigating the causal role of frontal theta oscillations in a clinical population [74]. There, a medium effect size of dz = 0.577 was found, which corresponds to a sample size of *n* = 20 per group at a power of 0.8 und an alpha level of 0.05. In total we will recruit *n* = 140 AUD patients to be included in this study.

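### The tVNS sample size of 40 per group does not follow from the means and SDs printed beside it, so the effect these arms are powered for is not established

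*Protocol article*

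**What the plan says.** The Sample size section of the protocol article bases the tVNS calculation on a cited study of tVNS in abstinent patients with alcohol use disorder. It opens with "According to the changes in the craving scores", sets 80% power and α = 0.05, and gives the source study's craving figures as "μ1 = 4.82; μ2 = 3.92; SD1 = 0.49; SD2 = 0.39". From these it concludes 40 per group, and after 20% attrition 50 per group. A separate effect size from a different study gives 20 per group for CLAM-tACS. The total is 140. The section gives no other effect size, SD, design factor, multiplicity adjustment or deliberate reduction of the effect for tVNS, and it does not state sidedness.

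**The concern.** The section presents 40 as the output of the stated inputs, so a reader can check it directly, and a two-point-zero standardised difference needs only a handful of patients per group. The line carries 100 of the 140 patients (2 × 50). If the printed SDs are right, they do not justify 40 per arm. If they are wrong or mislabelled, the standardised effect the tVNS arms were sized for appears nowhere, and a null result for active against sham tVNS could not be read against a known detectable effect.

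The wording adds an ambiguity. It refers to changes in craving scores but then describes the figures as the mean and SD of the scores. The text does not settle whether they are levels or changes, or whether the two means belong to two arms or two time points. That matters because the Statistical methods and analysis section plans an active-versus-sham comparison of treatment by time, and the relevant SD depends on the answer.

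**Working it through.** **Inputs, all from the Sample size section.** Means 4.82 and 3.92; SDs 0.49 and 0.39; power 0.80; α = 0.05, taken as two-sided because sidedness is not given; equal groups; attrition 20%.

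**What reproduces.** Attrition: 40 / (1 − 0.20) = 50. Total: 2 × 50 + 2 × 20 = 140. The total also shows that 40 is a per-arm figure and not the sum of two arms.

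**What does not reproduce: 40 itself.**

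- Difference: 4.82 − 3.92 = 0.90.
- Pooled SD: √[(0.49² + 0.39²) / 2] = √(0.3922 / 2) = 0.443.
- Standardised difference: 0.90 / 0.443 = 2.03.
- Normal approximation: n = (SD1² + SD2²)(1.960 + 0.842)² / 0.90² = 0.3922 × 7.849 / 0.81 = 3.80, so 4 per group.
- Two-sample t-test (noncentral t): n = 4.97, so 5 per group. Simulated Student-test power is 0.67 at 4, 0.80 at 5 and 0.89 at 6 per group. Welch's test gives 0.78 at 5 and 0.87 at 6, so it needs 6.
- With 20% attrition: 5 / 0.8 = 6.25, so 7 per group.
- Power at 40 per group with the printed inputs: above 0.9999.

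**Other readings tried (n per group; number of pairs for the paired test).**

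| Reading | n |
|---|---|
| One-sided 0.05, 80% power | 3 to 4 |
| Two-sided 0.05, 99% power | 9 to 10 |
| Two-sided 0.001, 80% power | 12 |
| Printed SDs are variances | 9 to 10 |
| SDs added together (0.88) | 16 to 17 |
| Paired test, correlation −0.9 to 0.9 | at most 10 |
| Effect halved | 16 |
| Effect cut to one third | 35 |
| Effect cut to one quarter | 61 |
| Printed SDs are standard errors, source groups of 10 | 39 |

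Only the last comes close to 40. There the SD would be 0.443 × √10 = 1.40. The result is sensitive to the assumed source group size: 20 per group if it was 5, and 58 if it was 15.

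**What 40 per group delivers.** Under a two-sided 0.05 two-sample t-test with 80% power, the detectable standardised difference is 0.634. In points this depends on which SD is true: 0.634 × 0.443 = 0.28 points with the printed SD. For 0.90 points to be the detectable difference, the SD would have to be 0.90 / 0.634 = 1.42.

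**The case against.** The best defence is that the arms may be correctly sized and only a label wrong. If the printed SDs are standard errors from groups of about 10, the calculation gives 39, practically the stated figure. This stands as a possibility and limits what can be concluded. It does not rescue the text: the source group size is not in the document, and the inputs would still be mislabelled.

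A second defence is that, for the printed effect, the error runs towards excess power. That is true if the SDs are right. But the section offers 40 as the result of these inputs and not as a deliberate margin above them.

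Third, the full protocol or analysis plan may hold more detail. That would answer a complaint about something left out. Here the article states a calculation in full, and it fails on its own figures.

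Three stronger readings are tempting and are not supported:

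- A reader might infer that the tVNS arms are eight times too large. The ratio 40 / 5 holds only if the printed SDs are correct, which is the point in doubt.
- A reader might infer that the article misstates the detectable effect. It prints no standardised effect and claims no detectable difference, so the effect is unestablished and not misstated.
- A reader might infer something about the size of the CLAM-tACS arms. Those rest on a different source and effect size, and nothing in this arithmetic bears on them.

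**Conclusion.** The point holds. The printed inputs give 5 per group by a two-sided two-sample t-test, or 4 by the normal approximation, against the stated 40. At 40 they give power above 0.9999, not 0.80. Sidedness and test are assumptions, but none of the conventional alternatives closes the gap. Either the size or the inputs are wrong, and the document alone cannot show which. The effect for which the tVNS arms have 80% power is therefore not established.

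The finding does not show that these arms are underpowered, or that they are oversized. The figure of 0.63 SD assumes a simple two-sample t-test, whereas the Statistical methods and analysis section plans linear mixed models of treatment by time. It is a reference value and does not describe the planned analysis.

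**What to change.** Reconcile the inputs with 40 against the source study and the original calculation. Correct any mislabelled SDs. State whether the means are levels or changes, whether they compare arms or time points, and which test and sidedness were used.

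If 40 does not come from these inputs, say so and report what it delivers. Suggested wording: *Under a two-sample t-test at two-sided α = 0.05, 40 completers per arm give 80% power for a standardised between-arm difference of about 0.63.* Add the equivalent in points once the SD is settled: 0.28 if it is 0.443, 0.90 if it is about 1.42.

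The cost is a check of the source and a rewrite of one or two sentences. Whether the number of patients should also change cannot be known until the inputs are reconciled.

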## Methods and analysis

### Study design

We will conduct a four-arm randomized controlled study at the Department of Psychiatry and Neurosciences, Charité – Universitätsmedizin Berlin. Detoxified patients with Alcohol Use Disorder (AUD) will undergo a meticulously structured Mindfulness-Based Relapse Prevention (MBRP) program consisting of six weekly group sessions supplemented with daily individual mindfulness practice sessions. Prior to and following treatment, participants will undergo comprehensive assessments including cognitive control evaluation using a Simon Go/NoGo (SGNG) task, assessment of cue-induced craving and a heartbeat discrimination task (HDT) as a marker for interoception, complemented by electrocardiographic measurements of heart rate and heart rate variability, alongside 32-channel electroencephalography (EEG) recordings. The pre and post treatment assessments will encompass various clinical and psychological metrics, including symptom and craving severity, as well as perceived loneliness and impulsivity. Long-term treatment effects will be evaluated through a follow-up assessment after three months, focusing on abstinence rates and alcohol consumption (Fig. 1).

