### Statistical methods and analysis

Our primary analyses will focus on the impact of active vs. sham stimulation (tVNS and CLAM-tACS) on neurobehavioral measures. To assess these effects, we will employ a linear mixed modelling approach to estimate the effects of treatment by time. Mediation will be assessed with path analyses.

First, we will investigate effects on cognitive function of augmented MBRP by administering the SGNG. Here, changes in SGNG behavioural inhibition pre to post treatment will be assessed, this further serves as a probe of the possible mediating effects of executive functioning on treatment success. We will further assess changes in cue reactivity as well as HDT interoceptive accuracy with multilevel modelling to allow for subject-specific effects [75]. Our study design also allows for the investigation of various levels of cue-induced effects, ranging from subjective indices of craving to physiological responses. Second, we will compare sham versus active stimulation + MBRP in terms of abstinence rates and drinking measures directly after and three months post treatment. We will investigate the course of clinical symptom severity as well as psychological measures before and after treatment as well as three months post treatment.

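### The CLAM-tACS arms are sized from a within-subject effect size, so the stated 80% power is not supported for the planned comparison of active with sham between arms

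*Protocol article*

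**What the plan says.** The Study design section sets out parallel arms: "We will conduct a four-arm randomized controlled study". The Statistical methods and analysis section names the main comparison: "Our primary analyses will focus on the impact of active vs. sham stimulation (tVNS and CLAM-tACS) on neurobehavioral measures". It gives the model as well: "we will employ a linear mixed modelling approach to estimate the effects of treatment by time".

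The Sample size section treats the two stimulation methods separately. For tVNS it arrives at 40 per group and then adds for drop-out: "With an attrition rate of 20%, final estimated sample size is" 50 per group. For CLAM-tACS it relies on an earlier study: "There, a medium effect size of dz = 0.577 was found, which corresponds to a sample size of" 20 "per group at a power of 0.8 und an alpha level of 0.05". It names neither the test nor its sidedness and mentions no attrition for these arms. The total is 140 "AUD patients to be included in this study".

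**The concern.** dz is the mean of paired differences divided by the standard deviation of those differences. It suits a comparison in which each person serves as his or her own control. A treatment-by-time effect in a parallel trial is a difference in change between two separate groups. Its variance contains a contribution from each arm, so for the same standardised effect it needs far more people per group than a paired test does.

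The sample size is therefore attached to a different comparison from the one the analysis section calls primary. At stake is whether the active-versus-sham contrast for CLAM-tACS, the arm through which the Background section approaches the causal role of frontal midline theta, has the power the article gives it.

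**Working it through.** **Inputs from the protocol article.** dz = 0.577, 20 per group, power 0.8, alpha 0.05, and 20% attrition in the tVNS calculation (all from Sample size); randomised parallel arms (Study design); active versus sham, treatment by time (Statistical methods and analysis). The split between arms is inferred: 2 × 50 + 2 × 20 = 140.

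**Step 1: reproduce the stated 20.** For a paired t-test the noncentrality parameter is dz × √n, with n − 1 degrees of freedom. At n = 20 it is 0.577 × √20 = 2.580.

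| Test at alpha 0.05, effect 0.577 | Power at 20 (per group) | n for 80% power |
|---|---|---|
| Paired, one-sided | 80.0% | 20 |
| Paired, two-sided | 68.7% | 26 |
| Two independent arms, one-sided | 55.8% | 38 per arm |
| Two independent arms, two-sided | 42.8% | 49 per arm |

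Only the first row gives 20 (n = 19 gives 78.1%). One-sidedness is an inference from this match.

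**Step 2: the planned contrast.** For two independent arms of n each, the noncentrality parameter is d × √(n/2), with 2n − 2 degrees of freedom. Assume that 0.577 is the between-arm difference in SD-of-change units.

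- n = 20: 0.577 × √10 = 1.825 on 38 degrees of freedom; two-sided power 42.8%. The difference detectable with 80% power is about 0.91.
- n = 49: two-sided power 80.7% (n = 48 gives 79.9%).

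**Step 3: attrition.** The tVNS figure follows 40 / 0.8 = 50. No such step is made for CLAM-tACS. The same 20% would leave 20 × 0.8 = 16 per arm: 0.577 × √8 = 1.632 on 30 degrees of freedom, two-sided power 35.2%, detectable difference about 1.02.

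**Step 4: does the effect scale rescue it?** The article gives no pre-post correlation r, so r is an assumption here.

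- *Convert dz to raw-SD units, then adjust for baseline.* The raw-SD effect is 0.577 × √(2(1 − r)). Dividing by √(1 − r²) for the adjustment gives 0.577 × √(2/(1 + r)). At r = 0.3 this is 0.716 and two-sided power at 20 per arm is about 60%. At r = 0.8 it is 0.608 and power is about 47%.
- *Reread 0.577 as a between-arm difference in raw-SD units.* At r = 0.8, change scores give 0.577 / √0.4 = 0.912 and power of about 80%; baseline adjustment gives 0.577 / √0.36 = 0.962 and about 84%. At r = 0.5 the powers are 43% and 54%.

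**The case against.** The strongest reply is that dz does not determine any between-arm effect. The cited study is not at hand, the conversion depends on a correlation the article does not give, and a mixed model with repeated measures can be more efficient than a plain two-sample test. That stands to this extent: 43% is conditional and should not be read as the trial's actual power. It does not restore the 80%. The gain from repeated measures is already used when 0.577 is expressed in SD-of-change units, and baseline adjustment after conversion gives 47% to 60% over the correlations tried. About 80% is reached only by rereading the effect as a raw-SD between-arm difference with a correlation near 0.8, and the article states neither.

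A second reply is that the CLAM-tACS section plans to examine phase-locking and theta amplitude during stimulation, where a within-person effect size is natural. That is fair, and it means the question about theta does not rest on the between-arm contrast alone. But the size is given per group and the analysis section makes active versus sham primary for CLAM-tACS too. Even a paired test, if two-sided, has only 68.7% power at 20.

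Three further inferences go beyond the document. A reader might take 35% as the power under the plan's own attrition; the 20% is stated only for tVNS, so carrying it over is an extension. A reader might take the one-sided test as declared; it is not. And a reader might infer that a null result would be presented as evidence against a causal role of theta; nothing in the article says so.

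**Conclusion.** The concern holds. The stated 80% belongs to a paired comparison, apparently one-sided, and is not supported for the between-arm contrast that the article calls primary. The mismatch itself needs no assumption beyond the meaning of dz and the stated design. Its size does: about 43% two-sided (56% one-sided) at 20 per arm if 0.577 carries over in SD-of-change units; 47% to 60% if it is converted and baseline-adjusted with assumed correlations of 0.8 down to 0.3; about 35% if, in addition to the first assumption, 20% of these patients are lost. The missing attrition allowance is a separate, smaller inconsistency within the same section, and it rests on the inferred 50/50/20/20 split.

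**What to change.** Keep the 140 patients and replace the CLAM-tACS sentence in Sample size. The new text should name the between-arm test and its sidedness, the scale on which the effect is expressed (with any correlation assumed), the attrition assumed for these arms, and the resulting power or detectable difference. On the SD-of-change reading with a two-sided test, that would be about 43% power for 0.577 and a detectable difference of about 0.91 at 20 per arm, or about 35% and 1.02 if 16 remain. Remove the description of this comparison as 80% powered, and say that it will be reported as an effect with a 95% confidence interval. If the dz calculation was meant for the within-person theta analysis, say so and attach it there.

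The cost is a few lines of text and a less favourable stated power; no patients are added.
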